### Data analysis

#### Sample size calculation

We aim to identify a small to moderate effect of the intervention on the patients’ assessment of experienced SDM (Cohen’s *d* of 0.3). Although the existing empirical findings are subject to uncertainty, this effect seems both practically relevant and realistic [12]. To identify this effect in a two-sided individual-level parallel group trial with an alpha error probability of 0.05 and a power of 0.80, a total sample of 352 participants would be needed. If an intra-class correlation coefficient of 0.05 is expected and three clinics are measured at four time points each (resulting in a total of 12 clusters; see Fig. 1), around 100 participants per cluster are necessary to maintain the specified alpha and beta error levels of 0.05 and 0.20, respectively [73, 74]. In order to be able to deal flexibly with frequently encountered issues (e.g., unequal-sized clusters, incomplete participant responses), we aim to recruit 360 participants at each time point across all clinics and 1440 participants in total.

As part of the process evaluation, we aim to conduct approx. *N* = 8–15 interviews with different HCPs per clinic. Participant observation will be conducted bi-weekly for 2 to 4 h per clinic. These are estimates and final sample sizes for qualitative data collection will be informed by theoretical saturation.

#### Analysis plan

##### Phase 1

The audio-recordings of cognitive interviews in phase 1 will be transcribed and imported into MAXQDA software (VERBI GmbH, Berlin, Germany). They will be analyzed drawing on the principles of content analysis [75].

##### Phase 2

Data will be entered by members of the research team consecutively, checked for range of data values and possible inconsistencies, and stored at secured servers of the department of the research team. Data will be analyzed using a mixed linear model with a random effect for clinic, a fixed effect for the time interval, and a fixed effect for the intervention effect [76]. An additional analysis will be performed to test for a possible interaction between intervention and time interval. If participant characteristics vary across clinics/time intervals, they will be used as participant-level covariates in the analysis model. In the case that a random effects model is not estimable (e.g., non-convergence due to the relatively low number of clinics), a fixed effects model will be used. Missing data patterns will be analyzed and dealt with adequately (e.g., by using maximum likelihood estimation). Two-sided testing will be applied throughout, and findings with an alpha error rate below 0.05 will be considered statistically significant.

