Temporality	Beginning of implementation phase in respective clinic	First coaching should be within 4 weeks after training	Throughout implementation phase in respective clinic with start at beginning of phase	Throughout implementation phase in respective clinic with start after HCP training	Beginning of implementation phase in respective clinic	Throughout implementation phase in respective clinic
Dose	2 h training	Two audits with oral and written feedback per HCP	Initial setup of material in different clinic areas, need-based restocking	Initial setup of material in different clinic areas, need-based re-stocking	Short oral presentation of new documents in team meetings, combined with email to staff members	Two to three meetings of approx. 60 min per clinic
Justification	[23, 25, 55, 56, 81] and pilot study [17, 18, 45]	[57] and pilot study [17, 18, 45]	[37, 58] and pilot study [17, 18, 45]	[82] and pilot study [17, 18, 45]	Pilot study [17, 18, 45]	Pilot study [43, 44]

*Inner setting = cluster level

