#### Critical reflection of current organization of multidisciplinary team meetings (MDTMs)

In order to integrate SDM better into existing workflows at MDTMs, quality improvement meetings will be held with the leading physicians of clinics and members of the clinical teams responsible for the MDTMs to evaluate and possibly re-organize existing MDTMs. The first meeting will follow the same guideline across all clinics. Subsequent changes will be developed in the process and hence might vary from clinic to clinic.

As described in the CFIR [42], slight adaptations of the implementation components over the course of the study are possible, in order to reflect real-world differences in clinic organization and to take into account the nature of implementation research [60].

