#### Outcome evaluation

The outcome evaluation will consist of four measurement points (i.e., baseline, 8 months, 16 months, 24 months). Each measurement point will consist of an assessment phase of 2 months. Due to the design of this study, different samples of individual patients will contribute to each measurement point (no follow-up assessment: independent samples). Clinical staff working at the clinics at the time of data collection will contribute to each measurement point (combination of new and previously surveyed participants with follow-up assessments: partly dependent samples). Patients will be recruited consecutively in the three clinics at all measurement points by a researcher of the study team. They will be approached individually (e.g., after registration at the front desk for outpatients, in wards for inpatients). Patients can participate in this study in three ways: (a) filling in the SDM-Q-9 after the encounter with the HCP, (b) agreeing to the encounter being audio recorded in order to be assessed using the Observer OPTION^5^ measure, or (c) both. The researcher will ask each patient for informed consent. The measures addressing the HCPs’ perspective will be administered in each clinic directly before the intervention program starts and at all consecutive measurement points (i.e., baseline, 8 months, 16 months, and 24 months for clinic 1; 8 months, 16 months, and 24 months for clinic 2; 16 months, and 24 months for clinic 3). All HCPs working at the respective clinic will be invited to fill in the questionnaires (complete enumeration).

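### The constant-effect model gives the longest exposure a negative weight, and the planned interaction with calendar interval has little power to show an effect that changes with time since roll-out

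*Protocol article*

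**What the plan says.** The protocol article, Analysis plan, Phase 2, specifies a "mixed linear model with a random effect for clinic, a fixed effect for the time interval, and a fixed effect for the intervention effect". It names a fallback: "In the case that a random effects model is not estimable (e.g., non-convergence due to the relatively low number of clinics), a fixed effects model" is to be used. The one planned check on whether the effect changes is "An additional analysis will be performed to test for a possible interaction between intervention and time interval". The time interval there is the same calendar factor as in the main model. No term for time since roll-out is given.

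On the layout, Sample size calculation says that "three clinics are measured at four time points each (resulting in a total of 12 clusters; see Fig. 1". Outcome evaluation says the staff measures are "administered in each clinic directly before the intervention program starts and at all consecutive measurement points". It then lists the survey points clinic by clinic: "baseline, 8 months, 16 months, and 24 months for clinic 1; 8 months, 16 months, and 24 months for clinic 2; 16 months, and 24", where the entry cut off at the end belongs to the third clinic.

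On delivery, Table 1 schedules patient information material and decision aids "Throughout implementation phase in respective clinic with start after HCP training". For changes to the multidisciplinary team meetings, the text says "Subsequent changes will be developed in the process and hence might vary from clinic to clinic". The same section allows slight adaptation of components during the study.

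**The concern.** A stepped wedge compares clinics that have started with clinics that have not, and it also uses clinics already treated as references for those that start later. If the effect is the same at every exposure time, this does no harm. If it grows or fades, a clinic treated for a long time becomes a distorted reference. One common coefficient is then not an average of the exposure-specific effects; it can put negative weight on some of them.

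Some components run through the whole implementation phase and may be adapted, so growth is possible. Staff turnover between measurement points makes fading possible too. An effect of the size the trial was designed for could then be reported as much smaller or much larger than its average over exposure. The stated safeguard is on a different time scale from the one that matters here.

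**Working it through.** **Inputs.** Three clinics, four measurement points, ICC 0.05, d = 0.3, two-sided alpha 0.05, about 100 patients needed per clinic-period, target 360/3 = 120 (all from Sample size calculation). Roll-out is inferred from Outcome evaluation: clinic 1 is 0,1,1,1; clinic 2 is 0,0,1,1; clinic 3 is 0,0,0,1. Effects are in SD units, and power is by normal theory.

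**Step 1: the plan's own figures.** A two-sample t-test for d = 0.3 needs 352 in total, as stated. The stepped-wedge design effect with one baseline, three steps, one measurement per step and n = 100 is

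[1 + 0.05(300 + 100 − 1)] / [1 + 0.05(150 + 100 − 1)] × 3(0.95) / [2(3 − 1/3)] = (20.95/13.45) × 0.534 = 0.832.

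Then 352 × 0.832 / 3 = 97.7 per clinic-period, which matches the stated figure of about 100.

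For the planned model, the closed-form variance in this layout is 3σ²(σ² + 4τ²) / (4σ² + 10τ²), with τ² = 0.05 and σ² = 0.95/m.
- m = 100: σ² = 0.0095, SE = 0.105, power 0.81.
- m = 120: σ² = 0.00792, SE = 0.096, power 0.88.

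**Step 2: weights under the fixed-effects fallback.** The estimate is Σ r·y / Σ r², where r is the treatment indicator minus its clinic mean, minus its period mean, plus the grand mean.
- Clinic 1: −0.250, 0.417, 0.083, −0.250
- Clinic 2: 0, −0.333, 0.333, 0
- Clinic 3: 0.250, −0.083, −0.417, 0.250

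Σ r² = 0.833. Summing over treated cells by exposure:
- first: (0.417 + 0.333 + 0.250)/0.833 = 1.2
- second: (0.083 + 0)/0.833 = 0.1
- third: −0.250/0.833 = −0.3

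**Step 3: weights under the random-effects model.** Generalised least squares with ICC 0.05 and m = 120 gives 1.17, 0.11 and −0.28. The third weight is negative at every ICC tried, from about −0.07 at ICC 0.001 to −0.29 at ICC 0.10. No effect curve is needed for this step.

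**Step 4: the planned interaction.** At baseline no clinic is treated and at 24 months all are, so the 24-month effect is aliased with the period. The saturated model has rank 6 for 7 columns, and only the 8- versus 16-month contrast is estimable (1 df, SE 0.164). Its weights on first, second and third exposure are −0.57, 0.43 and 0.14.

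**Step 5: expected results.** The curves are illustrative, because the documents give none. Example for 0.15/0.30/0.45: 1.173(0.15) + 0.109(0.30) − 0.282(0.45) = 0.082. The interaction contrast has expectation −0.568(0.15) + 0.432(0.30) + 0.137(0.45) = 0.106.

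| Effect at 1st/2nd/3rd measurement | Expected constant-effect estimate | Power of its test | Power, planned interaction | Power, 2-df exposure-time test |
|---|---|---|---|---|
| 0.30/0.30/0.30 | 0.30 | 0.88 | 0.05 | 0.05 |
| 0.25/0.30/0.35 | 0.23 | 0.66 | 0.06 | 0.08 |
| 0.20/0.30/0.40 | 0.15 | 0.36 | 0.07 | 0.20 |
| 0.15/0.30/0.45 | 0.08 | 0.14 | 0.10 | 0.41 |
| 0/0.45/0.45 | −0.08 | 0.13 | 0.34 | 0.99 |
| 0.45/0.30/0.15 | 0.52 | above 0.99 | 0.10 | 0.41 |

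All curves average 0.30.

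**Step 6: the exposure-time model.** Period effects plus three exposure indicators, with a random clinic effect, have full rank (7 of 7). The SEs of the three effects are 0.10, 0.15 and 0.22. The SE of their average is 0.148.

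**The case against.** Four points on the other side deserve weight.

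- **The planned test is not blind.** A reader might infer from the aliasing at 24 months that the interaction cannot detect a changing effect. The calculation does not support that. At 8 months only first-exposure data exist and at 16 months first and second, so the contrast partly follows exposure, and its power reaches 0.18 for 0/0.30/0.30 and 0.34 for 0/0.45/0.45. What stands is the wrong time scale, a single contrast and low power for gradual change.
- **The documents do not say the effect builds up.** Much of Table 1 is front-loaded: training and document revision come at the start, first coaching should follow within 4 weeks, and patient activation starts with the phase. The remark on team-meeting changes concerns differences between clinics as much as change over time. Growth is therefore possible, not expected, and an estimate near zero arises only with steep curves. With a plateau by the first measurement there is no bias, and 0.27/0.30/0.33 gives 0.26.
- **The remedy is weak on its own.** Third exposure is seen in one cell only, clinic 1 at 24 months. This argues for a supplement, not a replacement. The calendar interaction also answers a legitimate separate question and need not be removed.
- **An article condenses, and a SAP may add models.** Missing sensitivity analyses would be no finding in themselves. The point here is narrower: the article does state a check for a changing effect, and it states it on a scale that serves poorly in this layout.

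**Conclusion.** The point holds as a worthwhile improvement to the stated analysis; it does not show that the primary model is invalid. The negative weight on the longest exposure follows from the design and the model: about −0.28, or −0.3 under the fallback. How far it matters depends on an unknown curve, from no bias if the effect is constant to an expected 0.08 instead of 0.30 for 0.15/0.30/0.45, and 0.52 for the reverse. The planned interaction would seldom warn of gradual change (power 0.06 to 0.10 for the gradual curves tabulated).

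This rests on the inferred roll-out, the protocol's ICC and target size, equal cells, and normal-theory power, which ignores the further loss from having only three clinics.

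**What to change.** Keep the constant-effect model as primary, and the calendar interaction if wanted. Add a prespecified supplementary model with indicators for the first, second and third measurement after roll-out in each clinic. Report the exposure-averaged effect and the 2-df test of exposure heterogeneity beside the constant-effect estimate. State that the constant-effect estimate mainly reflects the first measurement after roll-out and does not by itself support conclusions about later effects.

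The work is one extra model, one table and one sentence of interpretation. The statistical cost should be stated too. Power for an average of 0.30 is about 0.53, against 0.88 for the constant effect, and about 0.30 if a t reference with 3 df is used (12 clinic-period cells minus 9 parameters with fixed clinic effects). The third-exposure effect cannot be separated from anything particular to clinic 1 at 24 months.

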### Setting

The study will be carried out in three clinics at a university hospital’s comprehensive cancer center in Germany: Department of Medical Oncology, Department of Gynecology, and Department of Oral and Maxillofacial Surgery. Conducting the study in three clinics within the same center allows for controlling the influence of outer setting to a certain degree [53]. These clinics were chosen because the heads of department expressed willingness and interest in implementing SDM in their clinics. They consented to participate in the study before randomization. Active promotion of a culture change towards SDM by the heads of department was identified as a key facilitator for the implementation of SDM in the previously conducted pilot study and has also been described in the literature [54].

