### Participants

Participants of this study will be both patients and HCPs. Inclusion criteria for participating patients are (a) being diagnosed with a neoplasm (ICD 10: C00-D49), (b) receiving inpatient or outpatient treatment at one of the participating clinics, (c) being at least 18 years of age, and (d) speaking German. Severe cognitive impairment is an exclusion criterion. Participating HCPs are the physicians and nurses working at the respective clinics. No exclusion criteria apply for HCPs.

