### Measures and outcomes

The focus of the evaluation will be on implementation outcomes based on Proctor’s taxonomy [61]. The primary outcome will be the uptake of SDM measured by the patient-reported *9-item Shared Decision Making Questionnaire* (*SDM-Q-9*, [62]). The questionnaire was developed in German, and item development was based on nine process elements characterizing SDM [62]. Items are scored on a 6-point Likert scale, ranging from 0 (“strongly disagree”) to 5 (“strongly agree”). A SDM-Q-9 sum score (ranging from 0 to 100) is calculated with higher values indicating a higher extent of SDM. The SDM-Q-9 showed good psychometric properties [62], was used in a range of studies on SDM [63], and currently exists in 16 languages (www.sdmq9.org). The SDM-Q-9 will be administered at all clinics at baseline, 8 months, 16 months, and 24 months.

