
Additionally, basic demographic information will be assessed from study participants.

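### Covariates enter the primary model only if they are seen to vary across clinics or time intervals, so the model is set by observed imbalance and not by expected link to SDM-Q-9

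*Protocol article*

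**What the plan says.** The Analysis plan (Phase 2) gives one model, whose last fixed term is the one for the program: "Data will be analyzed using a mixed linear model with a random effect for clinic, a fixed effect for the time interval, and a fixed". A fallback follows: "In the case that a random effects model is not estimable (e.g., non-convergence due to the relatively low number of clinics), a fixed effects model" is to be used. Covariates are then handled by one conditional sentence: "If participant characteristics vary across clinics/time intervals, they will be used as participant-level covariates in the analysis model".

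The sentence names no characteristic, does not define what counts as varying, and does not mention association with the outcome. It acts on the analysis model itself and is not labelled a sensitivity analysis. On what is available to adjust for, Measures and outcomes says only: "Additionally, basic demographic information will be assessed from study participants".

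Three other statements bear on the point:

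- **Outcome.** "The primary outcome will be the uptake of SDM measured by the patient-reported" SDM-Q-9.
- **Sampling.** "different samples of individual patients will contribute to each measurement point (no follow-up assessment: independent samples" (Outcome evaluation).
- **Case mix.** The clinics are the "Department of Medical Oncology, Department of Gynecology, and Department of Oral and Maxillofacial Surgery" (Setting), and patients qualify by "receiving inpatient or outpatient treatment at one of the participating clinics" (Participants).

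**The concern.** Whether characteristics vary can be known only after recruitment. Clinics and staff are not blinded, and clinic plus date identifies the condition. The primary model is therefore chosen with the data in hand.

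The criterion is also the wrong one. Differences between clinics, and changes common to all clinics over time, are largely absorbed by the clinic and time-interval terms. What can bias a stepped wedge estimate is a change of case mix within a clinic, beyond the common time trend, in a characteristic that predicts SDM-Q-9. What gains precision is adjusting for predictors whether or not they are imbalanced. The rule targets neither.

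Case mix matters here because there are only three clusters, each measurement point draws new patients, and inpatients and outpatients are both eligible.

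**Working it through.** **1. The plan's own figures.** A two-sided t-test at d = 0.3, alpha 0.05 and power 0.80 needs 175.4, so 176 per arm and 352 in total, as stated. The stepped wedge design effect uses k = 3 steps, one baseline and one later measurement per step, ICC ρ = 0.05 and m = 100:

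[1 + ρ(km + m − 1)] / [1 + ρ(km/2 + m − 1)] × 3(1 − ρ) / [2(k − 1/k)] = (20.95 / 13.45) × (2.85 / 5.333) = 0.832.

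Then 352 × 0.8324 × 4 = 1172 observations, and 1172 / 12 = 97.7 per clinic-period, matching the stated figure of around 100. The covariate rule changes none of this. The target of 1440 gives 120 per clinic-period.

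**2. Weight of each clinic-period.** Outcome evaluation implies program starts after baseline, 8 months and 16 months for clinics 1, 2 and 3. With clinic and period effects fixed, the intervention estimate weights the 12 cell means as follows:

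| | Baseline | 8 mo | 16 mo | 24 mo |
|---|---|---|---|---|
| Clinic 1 | −0.3 | 0.5 | 0.1 | −0.3 |
| Clinic 2 | 0 | −0.4 | 0.4 | 0 |
| Clinic 3 | 0.3 | −0.1 | −0.5 | 0.3 |

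The largest absolute weight is 0.5. The squared weights sum to 1.20, so the SE at 120 per cell is √(1.20 × 0.95 / 120) = 0.097 SD.

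**3. Bias if a shifting predictor is not adjusted for.** Bias = outcome difference × shift in mix × weight. Assume inpatients and outpatients differ by 0.3 SD and the mix shifts by 20 percentage points in one cell of weight 0.5. Then 0.3 × 0.20 × 0.5 = 0.03 SD, which is 10% of the target and about 0.3 SE. If the same shift came with rollout in every clinic, the weight would be 1 and the bias 0.06 SD (20%). These are values with no adjustment, not values under the rule.

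**4. How often chance triggers adjustment.** If varying meant p < 0.05 (an assumption; the plan names no test), the chance that at least one of K truly balanced, independent covariates enters is 1 − 0.95^K: 14%, 23% and 40% for K = 3, 5 and 10. Testing clinics and periods separately gives 1 − 0.95^(2K): 26%, 40% and 64%.

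**5. Simulation of the rule.** Setting: 3 clinics × 4 periods × 120 patients, six candidate covariates, p < 0.05 screen across clinics or periods. All covariate inputs are assumed.

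| Situation (d = 0.3) | Rule | Always-on |
|---|---|---|
| Nothing truly varies; three predictors at 0.2 SD (R² = 3 × 0.04 = 0.12): power | 0.86 | 0.89 |
| One non-prognostic covariate differs by clinic; two predictors at 0.2 SD (R² = 0.08): power | 0.85 | 0.88 |
| All six covariates clearly differ by clinic (SD of clinic means 0.2–0.5): power | 0.83–0.85 | 0.83–0.85 |
| As above, one predictor shifted 0.4 SD in the weight-0.5 cell: bias (0.041 unadjusted) | 0.004 | 0.003 |
| Covariates fairly balanced between clinics: power | about 0.83 | about 0.87 |
| Covariates fairly balanced, with a shift: residual bias | 0.01–0.02 SD | about 0 |

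The 0.041 agrees with 0.2 × 0.4 × 0.5 = 0.04. Raising the predictors to 0.4 SD each widens the power gap to 0.86 against 0.98, but that needs R² = 3 × 0.16 = 0.48, too much to expect of demographics. A more modest R² of 0.05 or 0.10 would cut the SE by 1 − √(1 − R²) = 2.5% or 5.1%.

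**6. Type I error.** Following the rule mechanically gave 0.050–0.053. Picking the most favourable of the unadjusted, screened and fully adjusted models gave 0.063–0.089.

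**The case against.** The strongest reply is that the rule will in practice come close to the model one would want. If clinic differences are almost certain, nearly every covariate enters, and one admitted for a clinic difference also adjusts for its shift over time. The third and fourth rows of the simulation table bear this out. That stands, and it limits the harm to characteristics that happen to look balanced.

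Four further points have weight:

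- The trigger looks at patient characteristics, not at SDM-Q-9 or the effect estimate, so it does not by itself inflate type I error. The plan does not propose picking among models.
- The plan mentions no significance test, and the slash between clinics and time intervals could mean the 12 clinic-by-interval cells. On that reading the criterion would catch within-clinic shifts.
- Clinic is a random effect with three levels. If its variance is estimated near zero, between-clinic case mix is not fully absorbed, and adjusting for it does protect.
- Patients are blinded and recruited consecutively by a researcher of the study team, which reduces the scope for selection.

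It can also be said that covariate lists belong in an analysis plan that is not shown. A missing list would indeed be no finding. But the article states a selection rule, and an analysis plan that follows it keeps the condition even if it lists candidates and defines the trigger.

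**Conclusion.** The point holds in a limited form. The primary model is not fixed in advance, and its covariates are chosen by observed imbalance instead of expected prognostic value. The consequences are a data-dependent primary model, room for selective choice because the trigger is undefined, and a modest loss when a prognostic characteristic looks balanced: power of about 0.83 against 0.87, or residual bias of about 0.01–0.02 SD. These sizes rest on assumed covariate strengths, shifts and a p < 0.05 screen, since the article gives none of them.

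A reader might infer that the rule protects against nothing, leaves case-mix bias largely uncorrected, or inflates the false-positive rate. The documents do not support this. Covariates that enter because clinics differ also remove bias from shifts over time, and type I error stays near nominal when the rule is followed. Nor does the text say that a non-significant shift leads to exclusion. Adjusting for case mix is sensible in this design; the fault lies in the trigger.

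**What to change.** Delete the conditional sentence. Name in advance a short set of participant-level covariates expected to predict SDM-Q-9, and include them in the primary model whatever the observed imbalance. Candidates are age, sex and education, if these are among the demographics recorded, and inpatient or outpatient setting, which the recruiter knows. Report the unadjusted model as a sensitivity analysis, and label any adjustment prompted by observed imbalance the same way.

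A marker of appointment type should not be added to the set. It would be new data collection, and the program could affect it, since it may reorganise multidisciplinary team meetings.

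The cost is a sentence or two of plan wording, a few degrees of freedom out of 1440 observations, and a stated method for missing covariate values. The sample size does not change.

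### With three clinics, the random-intercept primary model does not hold its 5% level, and a fixed-effects fallback tied to estimability does not address this; clinic should be a fixed factor from the start

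*Protocol article*

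**What the plan says.** Under Analysis plan, Phase 2, the protocol article specifies a "mixed linear model with a random effect for clinic, a fixed effect for the time interval, and a fixed effect for the intervention effect". The exception follows: "In the case that a random effects model is not estimable (e.g., non-convergence due to the relatively low number of clinics"). Under that condition the analysis changes to fixed effects. The section does not say what happens when the model is fitted but the clinic variance comes out at zero. It does not choose between REML and ML for the primary model; maximum likelihood appears only as an example of handling missing data. On the error rate it says: "Two-sided testing will be applied throughout, and findings with an alpha error rate below 0.05 will be considered statistically significant".

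The Sample size calculation section assumes an ICC of 0.05 and three clinics at four time points. It states that about 100 patients per clinic and time point keep alpha at 0.05 and beta at 0.20, and sets a target of 360 per time point, which is 120 per clinic. On how the clinics entered the trial, the Setting section says: "These clinics were chosen because the heads of department expressed willingness and interest in implementing SDM in their clinics".

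**The concern.** The authors saw that three clinics are few, but tied the remedy to one symptom, a model that cannot be estimated. The more common difficulty is quieter: the model is estimated, with too small a clinic variance. The analysis then gives too much weight to comparisons between whole clinics, which differ for reasons unrelated to the program, and reports too small a standard error. Nothing in the stated rule reacts to this.

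At stake are the 5% level of the primary test and a choice between two primary analyses that can depend on how an optimiser behaves.

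**Working it through.** **Inputs.** From the Sample size calculation section: d = 0.3, two-sided alpha 0.05, power 0.80, ICC 0.05, 3 clinics × 4 time points, 100 or 120 patients per clinic-period. Independent patient samples at each time point come from the Outcome evaluation section. The same section measures staff directly before the program starts, from baseline, 8 and 16 months in clinics 1, 2 and 3, so one clinic crosses over per step. Total variance is set to 1. ICC values of 0.02 and 0.01 are assumptions used to show a range.

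**1. The plan's own figures.** Two groups: 2 × (1.96 + 0.842)² / 0.3² = 174.5, so 175 per arm; the t-test correction gives 176, and 2 × 176 = 352, as stated ("a total sample of 352 participants would be needed").

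For the stepped wedge, let s² be the variance of a clinic-period mean and τ² the clinic variance. The Hussey–Hughes variance for this layout reduces to

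Var = 3s²(s² + 4τ²) / (4s² + 10τ²).

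With 100 per cell, s² = 0.95/100 = 0.0095 and τ² = 0.05: 0.0285 × 0.2095 / 0.538 = 0.01110, SE 0.1053, power 0.813. The stated figure of about 100 per cell is reproduced.

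**2. Fixed clinic effects.** Letting τ² grow without limit gives Var = 1.2s². With 100 per cell: 0.0114, SE 0.1068, power 0.802. With 120 per cell, s² = 0.00792: SE 0.0975, power 0.868, against 0.876 for the random-intercept formula.

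**3. What a zero clinic variance does.** At τ² = 0, Var = 0.75s². With 120 per cell the nominal SE is √(0.75 × 0.00792) = 0.077, against 0.097 with fixed clinics. In information terms, within-clinic comparisons supply 1/1.2 = 0.833 of a total 1/0.75 = 1.333, so between-clinic comparisons receive 0.5/1.333 = 37.5% of the weight. At the true ICC of 0.05 they deserve 1 − 0.0963737²/0.0974679² = about 2%.

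**4. Rejection under the null.** 100,000 simulated null trials per setting, with the plan's model exactly true and no clinic-by-period variance. Wald test at 1.96 for the mixed model; t-test for fixed clinics.

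| ICC | Per cell | REML | ML | Fixed clinics | Variance estimated as zero, REML / ML |
|---|---|---|---|---|---|
| 0.05 | 100 | 6.5% | 8.0% | 5.0% | 5.5% / 10.0% |
| 0.05 | 120 | 6.4% | 7.7% | 5.0% | 4.7% / 8.4% |
| 0.02 | 120 | 7.1% | 9.1% | 5.0% | 10.9% / 19.2% |
| 0.01 | 120 | 7.6% | 9.6% | 5.0% | 19.0% / 31.9% |

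Repeat simulations agree to within a few tenths of a point.

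**5. Does the trigger catch it?** In 150 REML fits with a standard package (ICC 0.05, 120 per cell), 8 had zero clinic variance and all 8 were reported as converged. Of the 150 fits, 145 converged, so the 5 that did not (150 − 145) all had a positive variance. In a larger check, 86–100% of zero-variance fits were reported as converged. At ICC 0.05, 15–19% of zero-variance fits reject falsely.

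**6. How much of the excess comes from zero-variance fits?** At ICC 0.05 and 120 per cell: 0.47 of 1.35 points (35%) with REML and 1.12 of 2.69 points (42%) with ML. The rest comes from clinic variances that are positive but too small. If zero-variance fits were also sent to the fixed-effects model, rejection would still be about 5.9% (REML) or 6.5% (ML).

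**7. Corrections.** Satterthwaite degrees of freedom with REML leave 6.2–6.6% at ICC 0.05 and 6.3–7.2% at ICC 0.01, depending on how zero-variance fits are treated. Kenward–Roger, which also adjusts the standard error, gave 4.5%, 3.9% and 3.4% at ICC 0.05, 0.02 and 0.01 (120 per cell, residual variance treated as known).

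**The case against.** Several points on the other side are sound.

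- **Size.** At the protocol's ICC with REML, the excess is only about 1.5 points. A reader might take 9.5% as the plan's error rate. That figure needs ML and an ICC near 0.01, and the document states neither.
- **Cause.** A reader might infer that the model usually collapses to zero variance and that this explains the excess. At ICC 0.05 it happens in about 5–10% of trials and supplies a minority of the excess. At ICC 0.01 it supplies more than half.
- **The trigger.** Non-convergence is given as an example, so a zero-variance fit could be read as not estimable. The text does not say so, and step 6 shows that this reading would not restore 5%.
- **Small-sample methods.** REML versus ML and the degrees-of-freedom method can be left to a SAP. It would be wrong to say that no correction can rescue the random-intercept model: Kenward–Roger holds the level. It is conservative, with simulated power of 85.2% against 86.9% for fixed clinics at ICC 0.05 and 120 per cell. What the article does fix is the primary model and the condition for leaving it.
- **Volunteer clinics.** Their selection does not make a random intercept invalid. It only weakens the argument that a random effect supports generalisation to other clinics.
- **The remedy's limits.** A reader might infer that fixed effects guarantee 5%. They do so only without clinic-by-period variance. If 10% of the ICC lay at clinic-period level, rejection would be about 12–13% with fixed clinics against 14–15% with the random intercept. Changing the clinic term removes little of that error.

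**Conclusion.** The concern holds in this limited form. The stated primary test does not keep its 5% level with three clinics, and a fallback tied to estimability does not repair it. The excess at the protocol's ICC of 0.05 is about 1.4–1.6 points with REML and 2.7–3.0 points with ML, and it grows if the ICC is smaller. These figures rest on the plan's own model being true, one crossover per step, equal cell sizes and a Wald test without small-sample correction.

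The main cause at ICC 0.05 is underestimation of the clinic variance in general, with zero-variance fits as its extreme. The remedy is therefore to change the primary model; a wider trigger would not be enough. The plan's own fallback meets the nominal level under the plan's own assumptions and keeps the stated 80% power at ICC 0.05.

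**What to change.** In the Analysis plan, make clinic a three-level fixed factor in the primary SDM-Q-9 model, alongside time interval and intervention, and delete the switch based on estimability. Report the random-intercept model as a sensitivity analysis, fitted by REML with a small-sample correction that also adjusts the standard error, such as Kenward–Roger. State that formal inference applies to these three clinics, and that the 5% level assumes no clinic-by-period variance.

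Apply the same change only to secondary outcomes analysed with this same model. It does not suit the 2017/2020 patient-survey comparison. The staff measures would need adaptation, because their samples are partly dependent and they start at different times by clinic.

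**Cost.** The change takes about one sentence for the model and one for the sensitivity analysis. Power at d = 0.3 falls as follows:

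| ICC | Per cell | Random intercept | Fixed clinics |
|---|---|---|---|
| 0.05 | 120 | 0.876 | 0.868 |
| 0.05 | 100 | 0.813 | 0.802 |
| 0.01 (assumed) | 120 | 0.886 | 0.854 |
| 0.01 (assumed) | 100 | 0.829 | 0.786 |

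The 80% target is kept except in the last row, an ICC of 0.01 with only 100 per cell.
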